**12.2.1.1. Analysis Populations**

Two populations will be considered for analysis in this protocol, one based on the intent- to-treat principle and the other is based on patients who have received at least 1 dose of study medication. For all efficacy analyses, an intent-to-treat population will be analyzed. This population consists of all patients randomized to a treatment group, even

if the patient did not take the assigned treatment, did not receive the correct treatment, or did not otherwise follow the protocol. All enrolled patients who had both a baseline and at least 1 post baseline score will be included in the analysis of the questionnaire data.

All patients who take at least 1 dose of study medication will be included in the analysis of safety data. It will be assumed that patients who receive medication during Study Period II have taken at least 1 dose, unless it is documented otherwise.

The following investigator pooling algorithm will apply to the primary and all other analyses – investigative sites with less than 2 patients per treatment arm will be pooled with the next smallest investigative site until that pooled site has at least 2 patients per

treatment arm.

**12.2.1.2. Adjustment for Multiplicity**

All tests of significance in this study will be conducted at a 2-sided alpha level of 0.05, unless otherwise stated. The primary efficacy analysis will be performed on the original scale data. All other analyses will also be performed on the original scale data. No adjustments for multiple comparisons will be made. All tests of hypotheses will be considered statistically significant if the two-sided p-value is less than 0.05. No adjustments for secondary comparisons are needed since we are using a gatekeeper strategy to prevent multiplicity in the comparisons that are of the greatest interest.

***12.2.2. Patient Disposition***

The percentage of patients who discontinue for various reasons (that is, lack of efficacy, adverse event) and the percentage of patients who complete the double-blind period among all randomized patients will be calculated for Study Period II. The percentages of discontinuations for each reason will be compared between treatment groups using Fisher’s exact test.

***12.2.3. Patient Characteristics***

Patient characteristics (demographics and baseline psychiatric measures) will be summarized for all entered as well as all randomized patients. For randomized patients, comparisons of patient characteristics will be made across treatment groups using Fisher’s exact test for categorical data and using an analysis of variance (ANOVA) with treatment as an independent effect for quantitative data.

***12.2.4. Concomitant Therapy***

Concomitant medications during Study Period II will be tabulated and compared across treatment groups using Fisher’s exact test.

***12.2.5. Treatment Compliance***

Compliance will be tabulated at each visit during Study Period II. The percentage of patients who are compliant at all visits during Study Period II will be tabulated and compared across treatment groups using Fisher’s exact test.

***12.2.6. Primary Outcome and Methodology***

The primary summary measure, the CAARS-Inv:SV total ADHD symptom score as well as the Inattention subscale score, and Hyperactivity-Impulsivity subscale score, will be analyzed using a restricted maximum likelihood (REML)-based, mixed model repeated measures (MMRM) technique. The model will include the fixed, categorical effects of treatment, investigator, visit, and treatment-by-visit interaction as well as the continuous, fixed covariates of baseline (last of scores at Visit 1 and Visit 2) score and baseline score- by-visit interaction. The following covariance structures will be fit to the model: unstructured, heterogeneous toeplitz, heterogeneous autoregressive, heterogeneous compound symmetry and simple. The correlation structure converging to the best fit as measured by Akaike's Information Criterion will be used as the primary analysis. The Kenward-Roger approximation will be used to estimate denominator degrees of freedom. Significance tests will be based on least-squares means and Type III sum-of-squares. Analyses will be implemented using SAS PROC MIXED. The primary comparison is

the contrast between treatments at Visit 6 (12 weeks post-baseline). Secondary evidence of efficacy from the primary analysis will be based on the main effect of treatment and

the treatment-by-visit interaction terms from the MMRM analysis. This measure will be summarized separately during Study Period III. All statistical tests will be two-sided and will be conducted at the 5% significance level.

***12.2.7. Secondary Analyses of the Primary Outcome***

As supporting evidence, the CAARS-Inv:SV total ADHD symptom score as well as the Inattention subscale score, and Hyperactivity-Impulsivity subscale score, will be analyzed using a last observation carried forward (LOCF) analysis. Change from baseline to LOCF endpoint will be compared across treatments using an ANCOVA model with terms for baseline, treatment, and investigator.

***12.2.8. Gated Secondary Efficacy Analyses***

The first gated secondary objective is to assess the efficacy of atomoxetine therapy compared with placebo on the total score of the Adult ADHD Quality of Life -29 (AAQOL-29) using a treatment contrast from the repeated measures mixed effects model at the final post baseline visit. The repeated measures model will include the same terms as that used for the primary efficacy measure. This measure will be summarized separately during Study Period III.

The next gated secondary objective is to assess the efficacy of atomoxetine therapy compared with placebo on the subscales of the AAQOL-29 in the following order: Relationship; Life Productivity; Psychological Health; and Life Outlook using a treatment contrast from the repeated measures mixed effects model at the final post baseline visit. The repeated measures model will include the same terms as that used for the primary efficacy measure. These subscale measures will be summarized separately during Study Period III.

**12.2.8.1. Secondary Efficacy Analyses**

The secondary efficacy analyses will be conducted for the variables included in, but not limited to, those in Table LYDZ(b).3.

**Table LYDZ(b).3. Description of Secondary Efficacy Variables**

Analysis Variable Description

1. All post-baseline scores for:

a. CAARS-S:SV total ADHD symptom score and subscores

2. Change from baseline to endpoint for the following Total scores and subscores:

a. AAQOL-29

b. CAARS-S-SV

d. PGI-I

e. Habits Timeline Followback: (Alcohol, Nicotine, Caffeine, Marijuana, Drug)

f. Fagerstrom Test for Nicotine Dependence g. SASS

h. Driving Behavior Survey-S i. Driving Behavior Survey-O j. BRIEF-A

k. Epworth Sleepiness Scale l. Beck Anxiety Inventory

m. CGI-ADHD-S

n. MADRS

Post-baseline during Study Period II is defined as

Visits 3-6.

Difference between baseline and last observation on study drug (LOCF change scores). See notes on computations of total and subscores below.

3. Indicator variable for responders 3. Patients will be classified as responders according to 2 definitions:

a. 25% or greater decrease in ADHD symptoms as measured by the CAARS-Inv-SV total ADHD symptom score OR

b. Decrease on CGI-ADHD-S of 2 or more

4. Indicator variable for strong responders 3. Patients will be classified as strong responders according to the following definition:

a. 40% or greater decrease in ADHD symptoms as measured by the CAARS-Inv-SV Total

ADHD symptom score

5. Indicator variable for remitters 4. Patients will be classified as remitters according to the following definition:

a. Endpoint CGI-ADHD-S = 1 or 2

6. Indicator variable for drug compliance 5. Compliance rates will be compared across treatment groups overall and by visit.

Abbreviations: ADHD = Attention-Deficit/Hyperactivity Disorder; CAARS-Inv-SV = Conners’ Adult ADHD Rating Scale-Investigator Rated: Screening Version; CAARS-S-SV = Conners’ Adult ADHD Rating Scale-Self Rated: Screening Version; PGI-I = Patient Global Impression-Improvement; SASS

= Social Adaptation Self-Evaluation Scale; Driving Behavior Survey (Self-Report); Driving Behavior Survey (Other-Report); BRIEF-A = Behavior Rating Inventory of Executive Function-Adult Version; CGI-ADHD-S = Clinical Global Impressions-ADHD-Severity; MADRS = Montgomery-Asberg Depression Rating Scale ; LOCF = last observation carried forward.

Variables 1-5 will be summarized for Study Period II using the last of Visits 1 and 2 as baseline and Visits 3-6 as the post-baseline visits. Variable 1a will be analyzed during Study Period II using a restricted maximum likelihood (REML)-based mixed effects model, repeated measures technique as defined for the primary efficacy analysis. This variable will be analyzed over the course of Study Period II using a contrast from the repeated measures mixed effects model at the final post baseline visit. Additionally,

visit-wise efficacy will be assessed using contrasts from this model at each post baseline

visit. This variable will be summarized separately by visit during Study Period III.

Variables 2.a through 2.n will be analyzed using a fixed-effects analysis of covariance (ANCOVA) model with terms for baseline score, treatment, and investigator. These variables will be summarized separately during Study Period III.

Variables 3-6 will be compared across treatment groups during Study Period II and separately during Study Period III using a Fisher’s Exact Test.

Time to response and time to remission will be compared across treatment groups during Study Period II using the Kaplan-Meier Product limit estimator, with the test for treatment difference being based on the log-rank test.

Correlation between the AAQOL-29 total score and the CAARS-Inv:SV total ADHD symptom score will be computed using Pearson’s correlation co-efficient to assess the relationship between these two measures.

A Fisher’s Exact Test will be used to assess baseline smoking status as a predictor of response (a 25% decrease from baseline on the CAARS-Inv:SV total ADHD symptom score) and strong response (a 40% decrease from baseline on the CAARS-Inv:SV total ADHD symptom score ) to atomoxetine treatment compared with placebo. If sparse data exists, a Chi-Squared analysis may be used instead.

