**10.1.2.4. Patient Global Impression-Improvement (PGI-I)**

The PGI-I is a 7-point scale modeled after the CGI on which patients rate any change in their overall status that they had experienced since beginning the study drug. The score on this scale ranges from 1 (very much improved) to 7 (very much worse).

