**12.2. Statistical and Analytical Plans**

***12.2.1. General Considerations***

Statistical analysis of this study will be the responsibility of Eli Lilly and Company or an approved vendor of Eli Lilly and Company.

Treatment effects for all efficacy and safety variables will be evaluated based on a two- sided significance level of 0.05, and the interaction effects at 0.10. Any change to the data analysis methods described in the protocol will require an amendment ONLY if it changes a principal feature of the protocol. Any other changes in the data analysis methods described in this protocol will be documented in the Statistical Analysis Plan (SAP) prior to unblinding of the data. Such changes will not require protocol amendments. If changes to the data analysis methods described in the protocol are deemed necessary the justification for making such changes will be described in the clinical study report. Additional exploratory analyses of the data will be conducted as deemed appropriate.

Active treatment phase refers to the visit interval after randomization in which the placebo lead-in period is excluded. In all the analyses, baseline will be the latest non- missing observation across all the visits in the screening phase and the placebo lead-in period, before the active study drug begins. Endpoint will be the latest non-missing observation across all the post-baseline visits before.

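### PGI-I is assigned to a change-from-baseline ANCOVA with a baseline covariate, but it is first rated at Visit 3 and is itself a rating of change, so the analysis cannot be run under the baseline rule written for it

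*Protocol*

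**What the plan says.** The protocol specifies the PGI-I analysis in several places.

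- **Variable.** Table LYDZ(b).3 in Section 12.2.8.1 places PGI-I at item 2.d, under "2. Change from baseline to endpoint for the following Total scores and subscores". The description column defines these variables as "Difference between baseline and last observation on study drug (LOCF change scores").
- **Model.** The text after the table makes no exception: "Variables 2.a through 2.n will be analyzed using a fixed-effects analysis of covariance (ANCOVA) model with terms for baseline score, treatment, and investigator".
- **Baseline for these variables.** The same text assigns the assessments to each role: "Variables 1-5 will be summarized for Study Period II using the last of Visits 1 and 2 as baseline and Visits 3-6 as the post-baseline".
- **Who is analysed.** Section 12.2.1.1 says of the questionnaire data that "patients who had both a baseline and at least 1 post baseline score will be included".
- **What the scale is.** Section 10.1.2.4 describes a 7-point scale on which "patients rate any change in their overall status that they had experienced since beginning the study drug".
- **When it is collected.** Protocol Attachment LYDZ(b).1 marks PGI-I at Visits 3, 4, 5, 6 and 9. Visits 1 and 2 are blank.
- **Competing baseline definition.** Section 12.2.1 sets a rule meant for every analysis, with the start of active treatment as its cut-off: "baseline will be the latest non- missing observation across all the visits in the screening phase and the placebo lead-in period, before the active study".

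The synopsis and Section 6.2.2 also list PGI-I among the measures to be assessed by mean change from baseline to endpoint.

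**The concern.** A change score and a baseline covariate both need a baseline value, and the schedule provides none for PGI-I. The scale asks how the patient has changed since starting study drug, so it already measures change and has no meaningful value before the first dose. The blank schedule cells are therefore right and the analysis text is wrong.

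At stake is one named secondary efficacy objective. As written, the PGI-I comparison either has no eligible patients or rests on the difference between two improvement ratings. The analyst would have to choose a replacement that the protocol does not state. That choice of score, model and covariate should be fixed before unblinding.

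**Working it through.** The protocol states no sample size, power or effect for PGI-I; Section 12.1 says none can be computed. The check therefore compares the schedule with the baseline rules.

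**Step 1. Baseline rule in Section 12.2.8.1 (last of Visits 1 and 2; post-baseline is Visits 3 to 6).** Scheduled visits are from Attachment LYDZ(b).1.

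| Item 2 variable | Baseline window | Post-baseline window |
| --- | --- | --- |
| CAARS-S:SV, CGI-ADHD-S | 1, 2 | 3, 4, 5, 6 |
| AAQOL-29, Habits Timeline Followback, Epworth | 2 | 3, 4, 5, 6 |
| Fagerstrom, SASS, both driving surveys, BRIEF-A, Beck Anxiety | 2 | 4, 6 |
| MADRS | 1 | 4, 6 |
| **PGI-I** | **none** | **3, 4, 5, 6** |

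The table shows 13 item 2 variables. Twelve have at least one scheduled assessment in the baseline window; PGI-I alone has none. The slip is confined to one entry in a shared list.

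**Step 2. Inclusion rule in Section 12.2.1.1.** A patient needs a baseline and at least one post-baseline score. For PGI-I the first condition is never met, so 0 of about 440 randomised patients qualify.

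**Step 3. General baseline definition in Section 12.2.1.** Sections 7.1 and 9.1.1 say that patients assigned to atomoxetine may start it as early as Visit 2 or as late as Visit 4. The actual timing is withheld in a separate document. Taking each possibility in turn:

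| Active drug starts at | PGI-I ratings available as baseline | Later ratings in Study Period II |
| --- | --- | --- |
| Visit 2 | none | 3, 4, 5, 6 |
| Visit 3 | Visit 3 | 4, 5, 6 |
| Visit 4 | Visits 3 and 4 (latest: Visit 4) | 5, 6 |

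In the last two rows the formula returns a number. However, the value called baseline is a rating of change since blinded drug began after Visit 2, and the endpoint is a rating of change from the same origin. Their difference describes change after the lead-in rating, not change from baseline. It also treats Visit 3, and possibly Visit 4, as baseline, whereas Section 12.2.8.1 and its table count both as post-baseline.

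**Step 4. What the intended comparison must be.** Suppose every patient were given the same notional pre-treatment value c, meaning no change yet. The change score is then Y − c. A constant covariate is absorbed by the intercept, so the model becomes

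Y = intercept + treatment + investigator + error.

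The treatment contrast is that of the endpoint score itself, whatever c is. Analysing the endpoint score without a PGI-I baseline term is thus the natural reading of the objective.

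**The case against.** The case on the other side has five parts.

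1. **An absolute claim goes too far.** A reader might infer that no patient could be analysed under any reading. The documents do not support that. The zero is exact under the Visit 1 and 2 baseline written for these variables, while Section 12.2.1 formally admits a lead-in value. This stands. Equally, one cannot say that a Visit 3 or 4 rating will become baseline, because the start of active drug is not disclosed; it could.
2. **The difference of two ratings is not meaningless.** Both share an anchor, so the difference roughly reflects further change after the lead-in. This is fair. The defect is that it is not the change from baseline the plan names.
3. **The objective can be read charitably.** A scale that rates change does measure change, so Section 6.2.2 is loose rather than wrong. This largely stands. The real fault is the table entry and the baseline term, and the objective needs only alignment.
4. **The SAP may deal with it.** Section 12.2.1 lets non-principal analysis changes be recorded there before unblinding, and the SAP is not at hand. That makes correction easy, but the protocol did not leave this analysis open. It states variable, model, baseline and population, and they do not work together.
5. **A larger remedy is not needed.** A repeated measures model with CGI-ADHD-S as covariate would go beyond the defect, since the protocol plans LOCF ANCOVA for all item 2 variables. This stands.

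**Conclusion.** The PGI-I analysis is wrong as written and should be corrected. Under the baseline rule attached to these variables and the questionnaire inclusion rule, 0 of about 440 patients are analysable. Under the general definition, the number depends on the undisclosed start of active drug, and the resulting quantity is not change from baseline. The conclusion rests on the schedule, the description of the scale and the stated model; no outside figure is needed.

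The consequence is limited. PGI-I is an additional, ungated secondary measure with no power claim. A reader might infer damage to the main efficacy conclusions, but the documents do not support it: the primary CAARS-Inv:SV contrast and the gated AAQOL-29 tests do not use PGI-I. Nor does this call for a PGI-I rating at Visit 1 or 2, since the scale has no meaning before dosing.

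**What to change.** - In Table LYDZ(b).3, remove item 2.d from the change-from-baseline list and give PGI-I its own entry: the score at endpoint, defined as the last PGI-I at Visits 3 to 6.
- In Section 12.2.8.1, exempt PGI-I from the baseline-score term and analyse the endpoint score with treatment and investigator terms.
- In Section 12.2.1.1, exempt PGI-I from the need for a baseline score, so that one post-baseline rating suffices.
- In Section 6.2.2 and the synopsis, refer to the PGI-I score at endpoint rather than mean change from baseline.

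A repeated measures model over Visits 3 to 6, or a baseline severity covariate such as CGI-ADHD-S, is optional. If either is wanted, it should be specified before unblinding.

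The cost is wording only, with no new assessment, visit or data. By the protocol's own rule, the analysis change can go into the SAP before unblinding if it is not a principal feature; the objective wording can be aligned whenever the protocol is next amended. The clash between the two baseline definitions reaches beyond PGI-I and should be resolved separately.

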**6.2. Secondary Objectives**

***6.2.1. Gated Secondary Objectives***

The following two secondary objectives will be tested using the Gatekeeper strategy (Westfall 2001). Atomoxetine and placebo will be compared in a stepwise fashion in order as indicated below. Testing will stop when a measure fails to show statistical significance favoring atomoxetine (p<0.05) based on a 2-sided test of significance.

• To assess the efficacy of atomoxetine therapy compared with placebo on the total score of the Adult ADHD Quality of Life -29 (AAQOL-29).

• To assess the efficacy of atomoxetine therapy compared with placebo on the subscales of the AAQOL-29 in the following order: Relationship; Life Productivity; Psychological Health; and Life Outlook.

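### The gated AAQOL-29 scores are also tested by LOCF ANCOVA with no stop and no supportive label, so a score past the stopping point could be called significant

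*Protocol*

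**What the plan says.** Protocol Section 6.2.1 puts the AAQOL-29 total first, then Relationship, Life Productivity, Psychological Health and Life Outlook, in that order. Its rule is: "Testing will stop when a measure fails to show statistical significance favoring atomoxetine (p<0.05) based on a 2-sided test of significance".

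Section 12.2.8 names the method for each of these objectives: "using a treatment contrast from the repeated measures mixed effects model at the final post baseline visit". The synopsis says the same.

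Section 12.2.8.1 lists the AAQOL-29 again, as item 2.a of Table LYDZ(b).3, under "Change from baseline to endpoint for the following Total scores and subscores". The table defines that variable as an LOCF change score. The text after the table says: "Variables 2.a through 2.n will be analyzed using a fixed-effects analysis of covariance (ANCOVA) model with terms for baseline score, treatment, and investigator".

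On significance, Section 12.2.1.2 says "No adjustments for multiple comparisons will be made" and gives as its reason that "we are using a gatekeeper strategy to prevent multiplicity in the comparisons that are of the greatest interest". It also says: "All tests of hypotheses will be considered statistically significant if the two-sided p-value is less than 0.05". Section 12.2.1 sets the same level: "Treatment effects for all efficacy and safety variables will be evaluated based on a two- sided significance level of 0.05".

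Section 12.2.7 introduces the LOCF analysis of the CAARS-Inv:SV as supporting evidence. Section 12.2.8.1 gives the AAQOL-29 ANCOVA no such label.

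**The concern.** The protocol relies on the gatekeeper as its only multiplicity control, and the five AAQOL-29 scores are what it places in the gated sequence. Those same five scores are tested a second time by a different method at the full 0.05, whether or not the sequence has stopped. The general significance sentence then attaches the word significant to any of those results below 0.05.

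Two things are at stake. First, the false-positive rate for the AAQOL-29 scores as a family is no longer the one that the fixed sequence was meant to deliver. Second, about 32% of patients are expected not to complete 12 weeks (Section 12.1), so the MMRM and LOCF results can differ. A report could then show a stopped sequence next to an AAQOL-29 score described as significant, with no protocol sentence saying how to word it.

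**Working it through.** **1. The plan's own AAQOL-29 figure.** Section 12.1 gives power of 80%, 85% and 93% for the total score at effect sizes 0.325, 0.35 and 0.40. With n = 220 × 0.68 = 149.6 per arm and power = Φ(d·√(n/2) − 1.96), where √(149.6/2) = 8.649:

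- d = 0.325: Φ(2.811 − 1.96) = 80.3%
- d = 0.35: Φ(3.027 − 1.96) = 85.7%
- d = 0.40: Φ(3.460 − 1.96) = 93.3%

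These agree with the stated values. They describe one test of the total score at 0.05. The protocol states no familywise error rate for the AAQOL-29 scores.

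**2. The rules followed in order.** Suppose the MMRM contrast for the total gives p = 0.08 (an invented value). Section 6.2.1 stops. Section 12.2.8.1 still runs the ANCOVA on the total and the four subscores. If one of those gives p = 0.03, Section 12.2.1.2 calls it significant. No sentence says otherwise.

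**3. Size of the effect.** Inputs from the protocol: two-sided 0.05 for every test, five scores, stop at the first failure. Inputs not in the protocol, and therefore assumed: correlation r between subscale test statistics of 0.5 (range 0.3 to 0.8), correlation m between the MMRM and LOCF statistics for the same score of 0.8 (range 0.6 to 0.95), and a total equal to the standardised sum of the subscales. The setting is no AAQOL-29 effect, given that the gated sequence has been reached.

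Model:

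- MMRM subscale statistics S1 to S4 are standard normal with pairwise correlation r.
- The MMRM total is T = (S1 + S2 + S3 + S4)/√(4 + 12r).
- Each LOCF statistic is m × (MMRM statistic) + √(1 − m²) × E, where E is an independent set with the same correlation structure.

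The gated sequence makes an error only if T itself rejects, because it stops otherwise. The family makes an error if T rejects or any of the five LOCF statistics does. Results from 1,000,000 draws per setting, for results favouring atomoxetine (statistic above 1.96):

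| r, m | Gated tests alone | Family with ANCOVA | Stopped at total, some LOCF test p<0.05 | Stopped at total, LOCF total p<0.05 |
|---|---|---|---|---|
| 0.5, 0.8 | 2.5% | 8.8% | 6.3% | 1.4% |
| 0.3, 0.6 | 2.5% | 10.5% | 8.0% | 1.9% |
| 0.8, 0.95 | 2.5% | 6.0% | 3.5% | 0.7% |

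The columns add up: 2.5% + 6.3% = 8.8% in the central case.

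Counting both directions, the family rate is about 17.5% (12% to 21%) against 5.0%. The chance of a stop at the total with some LOCF p<0.05 is about 12.6% (7% to 16%). If all six tests were independent, the two-sided rate would be 1 − 0.95⁶ = 26.5%, so the correlations already reduce it considerably.

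**4. After the fix.** If only the gated MMRM tests can be declared significant, the family rate returns to 2.5% favouring atomoxetine (5.0% two-sided). Sample size and power do not change.

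**The case against.** The best defence is that the ANCOVA was never meant to be confirmatory. Section 12.2.8 ties each gated objective to the MMRM contrast. Efficacy on the AAQOL-29 is an objective only in Section 6.2.1; Section 6.2.2 mentions the scale only for its correlation with the CAARS-Inv:SV. Pairing MMRM with LOCF ANCOVA is routine in this protocol (CAARS-Inv:SV, CAARS-S:SV), and where it ranks the two, LOCF is supporting. The p<0.05 sentence can be read as a general nominal threshold. Section 12.2.1 also lets non-principal analysis changes be documented in the SAP, which is not at hand and may already settle the matter.

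Much of this stands, and it rules out stronger readings that a reader might infer. One is that nothing says which analysis decides the gated objectives: Section 12.2.8 does say. Another is that the ANCOVA can reopen or override the sequence: no sentence allows that. A third is to take 17.5% as the headline error rate. That figure counts results favouring placebo, whereas the sequence passes only results favouring atomoxetine.

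The defence does not remove the conflict. Section 12.2.1.2 covers all tests of hypotheses without exception, and its reason for making no adjustment is the gatekeeper that these extra tests bypass. The supportive label is present for one LOCF analysis and absent for this one. So this is stated text in conflict, and more than a detail left to the SAP.

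**Conclusion.** The point holds as an inconsistency that should be corrected before unblinding. The MMRM contrast decides the gated objectives, but the protocol's own rules would also allow an AAQOL-29 score beyond the stopping point to be called significant on the LOCF ANCOVA.

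In the direction that matters, this raises the AAQOL-29 family error from 2.5% to about 8.8%, conditional on the sequence being reached and on no AAQOL-29 effect. Most of the excess comes from the subscales; for the total score alone it is about 1.4 percentage points. The sizes rest on correlations that the protocol does not give, but the family rate was at least 6% at every setting tried. These figures also count every favourable LOCF p<0.05 as a claim, which is what Section 12.2.1.2 permits and what a supportive label would prevent. The primary endpoint's error rate is unaffected.

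**What to change.** Either remove AAQOL-29 from item 2.a of Table LYDZ(b).3, or keep it and add to Section 12.2.8.1 wording such as: *The LOCF ANCOVA of the AAQOL-29 total and subscales is supportive and its p-values are nominal. The MMRM contrast at Visit 6 alone decides the gated sequence, and no AAQOL-29 score past the stopping point is declared significant on any analysis.* If it is kept, also exempt this analysis from the p<0.05 sentence in Section 12.2.1.2.

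The cost is one table line or a few sentences before unblinding, with no change to data collection, sample size or power. What is given up is an unprotected second route to significance for the AAQOL-29 scores.
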